	**Effectiveness**									
		VO_2_ peak^a^			✓				✓	
		Maximal heart rate			✓				✓	
		Resting blood pressure			✓				✓	
		PO peak^b^			✓				✓	
		Borg RPE^c^			✓				✓	
		Handgrip strength			✓				✓	
		SCIM III^d^			✓				✓	
		SF-36^e^			✓				✓	

^a^VO_2_ peak: peak oxygen uptake.

^b^PO peak: peak power output.

^c^Borg RPE: Ratings of Perceived Exertion Scale.

^d^SCIM III: Spinal Cord Independence Measure III.

^e^SF-36: Short Form–36 Health Survey.

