#### Secondary Outcomes

##### Overview

The secondary outcome is the effect of the intervention on peak exercise capacity, handgrip strength, independence, and quality of life. Peak exercise capacity and strength parameters were chosen because they are important factors for improving quality of life [11,15] and independence [10,14]. Quality of life and independence were chosen because these parameters are integral to the overall rehabilitation goal of people with SCI [50]. Furthermore, the guidelines for the conduct of clinical trials for SCI [51] suggest using the Spinal Cord Independence Measure III (SCIM III) for functional assessments and the Short Form–36 Health Survey (SF-36) for quality-of-life assessments.

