##### Quality of Life

The SF-36 is the most commonly used questionnaire to assess quality of life in people with SCI and has been shown to be valid and reliable for this population [61]. The survey comprises 36 items across 8 domains. The score ranges from 0 to 100, with a higher score indicating a better quality of life [62]. As previously recommended [11,63,64], 2 items referring to “climbing stairs” were replaced with “going up stairs” (German: *Stufen überwinden*), and 3 items referring to “walking” were replaced with “going” (German: *fortbewegen*).

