#### Quantitative Analysis

Quantitative data analysis will be performed using SPSS. All data will be tested for normal distribution using the Shapiro-Wilk test. Study participant characteristics will be presented descriptively by calculating means and SDs for normally distributed variables. Median values and IQR will be calculated for skewed continuous variables, and absolute and relative frequencies will be calculated for nominal variables. Group differences at baseline will be calculated for independent samples using a 2-tailed *t* test, Mann-Whitney *U* test, or chi-square test depending on the distribution and level of measurement. At t_1_, normally distributed continuous variables will be analyzed using a mixed analysis of variance model to test for significant effects for group and time. For skewed continuous variables, Wilcoxon and Mann-Whitney *U* tests will be conducted to test the differences between the groups and between t_0_ and t_1_. The significance level will be set at *P*<.05. Absolute and relative frequencies will be reported for adherence and retention.

Feasibility will be assumed if (1) at least 66% of the training sessions (equivalent to 2 out of 3 sessions per week) are completed [43] and (2) the retention rate is at least 75% [67]. Exercise diaries will be analyzed in terms of the frequency, duration, and intensity of the training sessions. Safety will be assessed by comparing the number of study-related AEs or SAEs in the intervention group with that in the waitlist control group [68].

Spearman correlations will be used to assess the association between performance and strength outcomes and SCIM III and SF-36 outcomes. Subgroup analyses might be conducted for lesion level (high vs low paraplegia) and age. Missing data will not be imputed.

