### Conclusions and Implications

By using both qualitative and quantitative measures, the results of this trial will generate a comprehensive understanding of the limitations and strengths of the ParaGym mobile exercise app as well as possible solutions to address the limitations. In the next step, in addition to fixing technical issues, the app should be adapted according to the findings of this study. This could include the expansion of the exercise pool and the addition of more equipment to increase variability and meet the needs of more advanced users. Hence, this could lead to an increased intensity of exercise sessions, which might result in greater effectiveness. Furthermore, the app interface might need to be adjusted to improve the ease of use. Finally, users may desire more features, such as the opportunity to design individual workouts or the integration of gamification to visualize the training process and promote adherence.

This pilot study will provide important results that need to be considered in the planning of future trials with an updated version of the app, which would aim for a larger sample size, longer intervention duration, and more diverse target group. As other individuals who use wheelchairs may also benefit from using the app, a requirement analysis addressing a broader target group should be conducted. Subsequently, a full-scale multicenter trial [73] including a broader target group, for example, people with acute SCI, tetraplegia, or other impairments, should be undertaken. In addition, by solely including healthy adults with SCI, a large proportion of the population was excluded. The prevalence of secondary diseases, such as cardiovascular diseases, is higher in individuals with SCI than in able-bodied people [74,75]. Therefore, investigators of future trials should consider including individuals with secondary diseases to assess the safety of the intervention for this group as well. Finally, future trials should include follow-up measures to investigate long-term motivation and adherence. In the long term, a fully marketable version of the ParaGym app should be implemented to make it publicly accessible.

An additional application of the ParaGym app could be its incorporation into workplace health programs, offering an exercise program for individuals who use wheelchairs and individuals with high levels of sedentary time at work.

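### Preliminary effects are specified only as unadjusted significance tests on eight unranked measures, with no between-arm difference and interval, at about 15 randomised per arm

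*Protocol article*

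**What the plan says.** The Quantitative Analysis section sends each continuous outcome down one of two routes. Normally distributed outcomes are to be "analyzed using a mixed analysis of variance model to test for significant effects for group and time". For skewed outcomes, "Wilcoxon and Mann-Whitney *U* tests will be conducted to test the differences between the groups" and between the two visits. One threshold covers everything: "The significance level will be set at" P<.05. Multiplicity is not mentioned, and neither is a between-arm difference or a confidence interval. The descriptive summaries (means with SDs, medians with IQRs) are introduced for participant characteristics.

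The Overview under Secondary Outcomes gives four domains without ranking them: "The secondary outcome is the effect of the intervention on peak exercise capacity, handgrip strength, independence, and quality of life". The Effectiveness block of Table 1 has eight rows measured at both visits: VO2 peak, maximal heart rate, "Resting blood pressure", PO peak, Borg RPE, handgrip strength, SCIM III and SF-36. Maximal heart rate, blood pressure, PO peak and Borg RPE are not in the list of domains.

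On purpose, the Conclusions and Implications section says: "This pilot study will provide important results that need to be considered in the planning of future trials".

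**The concern.** The article commits to an output, the significance verdict, that does not fit its stated use. Planning a larger trial needs an estimated difference, an SD and a plausible range for the effect. A list of P values from about 15 per arm supplies none of these.

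Two things are at stake. With several unranked outcomes at one unadjusted level, the reader has no prespecified way to weigh a single P<.05 against the other results. And where a test is not significant, the verdict alone does not show whether the data exclude a useful effect or merely fail to detect one.

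**Working it through.** The article gives no power, effect size, SD or family-wise error rate, so there is no figure to reproduce. The total of 45 rests on earlier studies and usability recommendations (Sample Size).

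**Inputs**
- Measures: 8 rows (Table 1, Effectiveness); 4 domains (Secondary Outcomes, Overview).
- Level: 0.05 per test. Two-sided is assumed for the t1 tests; the article says it only for the baseline comparison, "using a 2-tailed *t* test, Mann-Whitney *U* test, or chi-square test".
- Randomised: 30, all at the GSU (Randomization), at 1:1 (Study Design), so about 15 per arm.
- Retention threshold: 75% (Quantitative Analysis). 0.75 × 15 = 11.25, so about 11 per arm.
- Assumptions not in the article: correlation between outcomes, correlation between baseline and t1, and effect size in SD units.

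**Chance of at least one false positive, one between-arm test per measure**

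For independent outcomes this is 1 − 0.95^m.
- m = 4 domains: 1 − 0.95^4 = 0.186
- m = 8 rows: 1 − 0.95^8 = 0.337

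For eight correlated outcomes, 20,000 trials were simulated with 15 per arm, equicorrelated normal data and one two-sided t test per outcome:

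| Assumed correlation | Chance of at least one P<.05 |
|---|---|
| 0 | 34% |
| 0.3 | 30% |
| 0.5 | 25% |
| 0.7 | 20% |

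The planned tests of time, the Spearman correlations and the optional subgroup analyses are not counted here.

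**Precision of a between-arm difference, in SD units**

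Comparison at t1 alone: half-width = t(0.975, 2n − 2) × √(2/n).
- n = 15: 2.048 × √(2/15) = 2.048 × 0.365 = 0.75
- n = 11: 2.086 × √(2/11) = 2.086 × 0.426 = 0.89

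Baseline adjustment multiplies this by about √(1 − r²), where r is the baseline-to-t1 correlation. A comparison of changes multiplies it by √(2(1 − r)). At n = 15:
- r = 0.8, adjusted: 0.748 × 0.600 = 0.45
- r = 0.8, change: 0.748 × 0.632 = 0.47
- r = 0.5, adjusted: 0.748 × 0.866 = 0.65
- r = 0.5, change: 0.748 × 1.000 = 0.75

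**Power for an assumed true difference of 0.5 SD**
- t1 comparison: 26% at 15 per arm, 20% at 11 per arm.
- Change comparison at r = 0.8, 15 per arm: 55%.
- Baseline adjustment at r = 0.8, 15 per arm: 60%.

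For the t1 comparison at 15 per arm, power is 12.5% for 0.3 SD and 56% for 0.8 SD.

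**The case against.** The strongest reply is that this is a secondary, preliminary analysis in a pilot. The decision rules in the article concern the primary outcomes: a SUS score of at least 70, at least 66% of sessions completed, and at least 75% retention. No rule ties P<.05 to a claim of effectiveness. The Strengths and Limitations section already concedes that the small sample limits conclusiveness. Unadjusted testing of secondary outcomes in a pilot is not an error in itself, and a mixed ANOVA does not stop anyone from reporting estimates, which a fuller plan might contain.

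Most of that is correct, and it rules out several stronger readings.

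- A reader might infer that effectiveness is to be judged by P<.05. The article does not say so.
- A reader might count about 16 outcomes by testing all eight SF-36 domains separately and splitting blood pressure into two. The Quality of Life section does say "The survey comprises 36 items across 8 domains", but it also describes a 0 to 100 score, and nothing says that the domains are tested one by one. The documented count is eight.
- A reader might conclude that a chance finding is likely. At eight measures and one between-arm test each, the figure is 34% at most.
- A reader might call every null result uninformative. The planned mixed ANOVA uses both visits, so its precision depends on a baseline correlation that the article does not state. At 0.8 the interval is clearly narrower than 0.75 SD.
- A reader might say that the variables are undefined. The Abstract identifies peak exercise capacity with VO2 peak, and the Handgrip Strength section defines the sum of the best values of both hands.

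What the reply does not remove is that the article fixes an analysis for the effects, that this analysis consists of significance tests, and that the P values are not labelled exploratory. A fuller document could add estimates, but the method stated here would still be poorly matched to its purpose.

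**Conclusion.** The point holds in limited form. Eight unranked effectiveness measures are to be tested at an unadjusted P<.05 with about 15 randomised per arm, and significance is the only effectiveness output specified.

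The chance of at least one false positive among the eight between-arm tests is up to 34%, and 25-30% at assumed correlations of 0.5 to 0.3. That is enough to make a single P<.05 weak evidence, without making one probable. At 15 per arm the interval half-width runs from about 0.45 SD (baseline-adjusted, assumed correlation 0.8) to about 0.75 SD (unadjusted). It is 0.89 SD unadjusted at 11 per arm, so a bare non-significant verdict tells a planner little. These figures assume two-sided tests and roughly normal data. The conclusion that estimates with intervals serve the stated purpose better does not depend on any particular correlation.

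**What to change.** In the Quantitative Analysis section:

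1. Make the between-arm difference, with its 95% CI and the SD, the main output for each effectiveness measure in Table 1.
2. Name the lead variable for each of the four secondary domains: VO2 peak, the handgrip sum, the SCIM III total and one stated SF-36 score. Treat the other Table 1 rows as supportive.
3. State that P values are exploratory, are not adjusted for multiplicity and will not be used to claim effectiveness.

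This changes wording and table layout only, and needs no further participants, visits or measurements. The small downside is that no significant effect can be headlined from this pilot.

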### Study Design

This pilot mixed methods block-randomized controlled feasibility trial with an allocation ratio of 1:1 for the intervention and waitlist control groups is conducted at the German Sport University Cologne (GSU), Germany. The trial was registered with the German Clinical Trials Register (DRKS00030370).

Participants will be recruited at the GSU and the SCI center at the BG (*Berufsgenossenschaft*; English: occupational insurance association) clinic Tübingen, Germany. Participants will be recruited at the GSU via the project newsletter, the project website, social media, and by contacting rehabilitation centers and spinal cord associations. The BG clinic in Tübingen will recruit among their patients.

Measurements will be conducted at baseline (t_0_) and after the intervention (t_1_; Table 1). The primary outcomes (feasibility, usability, and safety) will be assessed during the intervention and at t_1_. The secondary outcomes (peak exercise capacity, handgrip strength, independence, and quality of life) will be assessed at t_0_ and t_1_. As data collection at the BG clinic Tübingen will focus on the primary outcomes and owing to limited capacity, the ramp exercise test for evaluating peak exercise capacity and handgrip strength test will be conducted only at the GSU and not at the BG clinic Tübingen. After randomization and group allocation, participants in the intervention group will be provided with the ParaGym mobile exercise app and uptake a 6-week home-based training intervention. The participants will be instructed to complete 3 training sessions per week. For this cohort, resistance training for at least 2 days a week is recommended [2,6]. As the training sessions delivered by the app comprise not only strength but also aerobic and flexibility exercises, we decided to provide training sessions for 3 days instead of 2. Eitivipart et al [34] recommend 3 sessions for a minimum duration of 20 minutes per week over at least 6 weeks to achieve substantial outcomes. The waitlist control group will proceed with their usual care and receive access to the mobile app once they have completed the trial. After the 6-week intervention, participants in the intervention group will be interviewed over the phone to assess feasibility and usability. Subsequently, both groups will return to the study site (t_1_) for the SUS questionnaire and secondary outcome measures. The study design and planned participant flow are presented in Figure 3.

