#### Randomization

Only the 30 participants recruited at the GSU will be block randomized, stratified by the level (high vs low paraplegia) and completeness (complete vs incomplete paraplegia) of the SCI with a block size of 4. This will be done using Excel (Microsoft Corp). The randomization code will be released after the participant has completed all baseline measures. The randomization list will be password protected. Only JB and AL, who conduct the randomization and allocation, will have access to the list. No randomization is required at the BG clinic Tübingen, as data collection at that site focuses on the primary outcomes.

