### Measures

#### Primary Outcomes

##### Overview

The primary outcomes are feasibility, usability, and safety. Six weeks after commencing the intervention, semistructured interviews will be conducted via phone to investigate feasibility and usability. An interview guide was conceptualized based on interview domains and topics in similar studies [27,36,39-43]. The following topics will be addressed: (1) overall experience, (2) ease of use, (3) app functionality, (4) perceived safety, (5) technical functionality, (6) communication, (7) perceived effects and usefulness, (8) adherence and motivation, and (9) recommendation. The interviews will be audio recorded with the consent of the participants.

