##### Safety

The safety of the app-based exercise program will be determined based on the occurrence of intervention-related AEs and SAEs. Participants will be instructed to report any AEs or health-related interruption of the intervention within 24 hours. AEs and SAEs will be classified by the grade of severity based on the Spinal Adverse Events Severity System version 2 (SAVES-V2) scale [48] (Table 2) and expectance. The following AEs and SAEs can occur because of physical strain or are common complications after SCI and are, therefore, classified as expected AEs or SAEs: (1) autonomic dysreflexia, (2) pressure ulcers, and (3) shoulder pain [49].

**Table 2 table2:** Classification of adverse events (AEs) and serious adverse events (SAEs) based on the Spinal Adverse Events Severity System version 2 scale.

Severity of AE or SAE	Clinical impact
1	AE—no treatment
2	AE—outpatient treatment
3	SAE—inpatient treatment
4	SAE—life-threatening injury
5	SAE—death

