#### Sample Size

The aim is to recruit a total of 45 participants between November 2022 and January 2023: 30 participants at the GSU and 15 participants at the BG clinic Tübingen. As this is a pilot trial, the sample size was based on previous studies with similar aims and methods [27,28] and recommendations for usability testing [65].

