## Discussion

### Principal Findings

To the best of our knowledge, this is the first trial to investigate the feasibility, usability, and safety of a 6-week exercise program delivered by an intelligent mobile exercise app for individuals with paraplegia using qualitative and quantitative measures. As secondary outcomes, the preliminary effects of this program on peak exercise capacity, handgrip strength, independence, and quality of life will be assessed. As the app is currently at a prototype stage, technical issues compromising feasibility and usability might occur. Both the semistructured interviews and exercise diaries will provide detailed insights into the users’ experience with the app. This will help identify various aspects regarding the feasibility and usability of the exercise sessions, app’s interface, and app’s technical functionality, including intelligent personalization. Furthermore, users’ practical suggestions for improvement will contribute to drawing practical implications. These could include the following: (1) further adapting the app to meet the needs of the target group; (2) fixing technical issues; (3) improving the ease of use, (4) improving the design, intensity, and duration of the exercise sessions; and (5) improving the overall satisfaction with the app. Before integrating the exercises into the app, all exercises, including the exercise videos and descriptions, were tested and evaluated in terms of feasibility, usability, and comprehensibility by 10 workshop participants with paraplegia. Therefore, we expect these exercises to be feasible and usable. The program is expected to be safe, as a very low incidence of AEs has been reported during exercise trials with this cohort [49,71].

Similar mobile apps for promoting a healthy lifestyle in people with SCI have been shown to be feasible [27,28]. However, these apps were not declared to be at a prototype stage. In contrast to these already existing mobile apps, the ParaGym mobile exercise app delivers individualized training sessions without the need for exercise selection by the users or health care professionals. Thus, training sessions can be performed independently by people without specific knowledge of training and exercise. In fact, the most frequently mentioned suggestion for improvement of the WHEELS app [27] was related to personalization and better tailoring to the user’s needs and functional capabilities.

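### Safety, a primary outcome, is assessed by comparing adverse event numbers between app and waitlist with no denominator or measure of precision, which at this size cannot support a safety conclusion in either direction

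*Protocol article*

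**What the plan says.** The Overview under Primary Outcomes lists the primary outcomes: "The primary outcomes are feasibility, usability, and safety". The Safety section bases safety on which events occur: "The safety of the app-based exercise program will be determined based on the occurrence of intervention-related AEs and SAEs". It adds severity grading and a split into expected and unexpected events. The Quantitative Analysis section then gives the analysis: "Safety will be assessed by comparing the number of study-related AEs or SAEs in the intervention group with that in the waitlist control group".

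No denominator, interval, margin or acceptable rate accompanies that sentence. The other two primary outcomes have numeric criteria: 66% of sessions and 75% retention for feasibility, and a System Usability Scale score of at least 70 for usability.

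On size, the Sample Size section plans "30 participants at the GSU and 15 participants at the BG clinic Tübingen" and explains that "As this is a pilot trial, the sample size was based on previous studies with similar aims and methods". The Randomization section states: "Only the 30 participants recruited at the GSU will be block randomized". The Study Design section describes the trial as one "with an allocation ratio of 1:1 for the intervention and waitlist control groups". The only information on the expected event rate is in the Discussion: "The program is expected to be safe, as a very low incidence of AEs has been reported during exercise trials with this cohort".

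**The concern.** A comparison of event numbers between two very small groups has two weaknesses. If events are uncommon, similar or zero numbers in both arms are the likely result whether or not the programme adds risk, so a quiet result carries little information. If the app group is about twice the size of the waitlist group, raw numbers will tend to be higher with the app even when individual risk is the same, so an excess carries little information either.

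At stake is what can be reported for a primary outcome. The Conclusions and Implications section says the results should inform later trials with broader groups. Planners of those trials need to know how large a risk this pilot has ruled out, and the stated analysis does not tell them.

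**Working it through.** **Inputs from the article.** Total 45, made up of 30 at the university and 15 at the clinic. Only the 30 are randomised, 1:1, giving 15 app and 15 waitlist. There is no sample size calculation to reproduce; only 30 + 15 = 45 can be checked.

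**Assumptions.**
- All 15 clinic participants use the app, giving 15 + 15 = 30 app users against 15 controls. The text does not say this directly and Figure 3 is not shown. The 8 to 4 split among the first 12 enrolled (Table 3) is consistent with it.
- The article gives no event rate, so a range of control risks is used.
- Fisher's exact test, two-sided 5%, on participants with at least one event. This is a yardstick; the article names no test for adverse events.

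**Step 1: chance of missing a doubling.** For control risk p and app risk 2p, the miss probability is 1 − Σ Bin(a; n₁, 2p) · Bin(b; n₂, p), summed over all pairs (a, b) with Fisher P < .05.

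| Control vs app risk | 15 vs 15 | 30 vs 15 |
|---|---|---|
| 5% vs 10% | 99% | 99% |
| 10% vs 20% | 96% | 94% |
| 20% vs 40% | 89% | 79% |
| 30% vs 60% | 77% | 61% |
| 40% vs 80% | 55% | 28% |

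For control risks of 10% and 20% the range is 79% to 96%. At lower rates, the direction the article itself expects, a doubling is almost always missed. When events are common it is missed less often.

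Counting events instead of participants (Poisson counts, conditional binomial test), a doubling is missed 72% (15 vs 15) or 62% (30 vs 15) of the time at 0.5 events per control participant, and 44% or 30% at 1.0.

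**Step 2: what it takes to see a difference.** With no affected controls, Fisher P first falls below .05 at 5/15 app users (P = .042; 4/15 gives .10) or 8/30 (P = .038; 7/30 gives .077). A third or about a quarter of app users would have to be affected.

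**Step 3: raw numbers in unequal groups.** With equal risk p in both groups, P(A > B) for A ~ Bin(30, p) and B ~ Bin(15, p) is:

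| True risk in both groups | App shows more affected participants |
|---|---|
| 5% | 55% |
| 10% | 69% |
| 20% | 83% |
| 30% | 90% |

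The cause is group size alone: at 20%, the expected numbers are 30 × 0.20 = 6 and 15 × 0.20 = 3.

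**Step 4: what an interval would say.** With zero events in n users, the exact two-sided 95% upper limit is 1 − 0.025^(1/n).
- n = 30: 1 − 0.025^(1/30) = 11.6%.
- n = 15: 1 − 0.025^(1/15) = 21.8%.

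A true risk of 5% would give no events among 30 users with probability 0.95³⁰ = 21%.

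**The case against.** The strongest objection is that a reader might infer a rule that no significant difference will be taken as safe. The article contains no such rule. It says when feasibility will be assumed and when the app will count as usable, but has no matching sentence for safety. The 5% significance level is stated with the tests for continuous outcomes; the safety sentence is in the next paragraph and names no test. The comparison may well be descriptive, in which case the power figures are illustrations and not properties of the plan. This objection stands.

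A reader might also infer that a favourable result would lead to the app being opened to people with cardiovascular disease. The Conclusions and Implications section does not say that. It suggests that future trials consider including people with secondary diseases so that safety can be assessed in them.

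The trial is also a labelled pilot, not sized for adverse events, and the Strengths and Limitations section concedes that the small sample limits conclusiveness. Severity grading and interview questions on perceived safety add information beyond the comparison. Low power for rare events is therefore not an error in itself, and interval methods could sit in an analysis plan that is not shown.

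What survives is narrower. The article does fix the method for a primary outcome, and the method is a comparison of numbers. A descriptive comparison of raw numbers in groups this small and possibly unequal remains uninformative, as Step 3 shows without any test. The general caveat about sample size does not change the rule.

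**Conclusion.** The point holds in this form: the analysis stated for a primary outcome compares event numbers, without denominators or precision, in groups of 15 and 15 or possibly 30 and 15, and it cannot support a safety conclusion in either direction.

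The 79% to 96% miss rate depends on an assumed test and assumed control risks of 10% and 20%. It is about 99% at 5% and falls clearly lower once events are common. The 55% to 90% chance of a higher app count depends on all clinic participants using the app and on equal true risks of 5% to 30%. The upper limits of 11.6% for 0/30 and 21.8% for 0/15 depend only on the number of app users.

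This is a change that should be made. It does not call for a larger trial.

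**What to change.** In the Quantitative Analysis section, replace the comparison of numbers as the basis of the safety assessment with the following:

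- Report the proportion of app users with at least one AE and with at least one SAE, and events per completed session, each with an exact 95% confidence interval.
- Word the safety statement around the upper limit. For example, no SAE in 30 users leaves risks up to about 12% not excluded, and none in 15 leaves risks up to about 22%.
- Show the between-arm difference in proportions, with its interval, for the randomised university participants only and label it descriptive. Report the clinic cohort separately.
- State that absence of a difference between arms will not be taken as evidence of safety.

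The cost is a few sentences and a few exact intervals, with no new data or participants. The downside is a more modest safety claim.

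### The primary safety comparison is set as a raw number of events per group, with no count of affected participants and no denominator

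*Protocol article*

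**What the plan says.** Under Primary Outcomes, Overview: "The primary outcomes are feasibility, usability, and safety". The Safety section adds: "The safety of the app-based exercise program will be determined based on the occurrence of intervention-related AEs and SAEs". Events are then graded by severity and expectedness. The only statement of how the groups will be compared is in Quantitative Analysis: "Safety will be assessed by comparing the number of study-related AEs or SAEs in the intervention group with that in the waitlist control group".

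That section attaches absolute and relative frequencies to adherence and retention, but not to safety. It attaches no test to the safety comparison. The named tests belong to baseline differences ("Group differences at baseline will be calculated for independent samples using a 2-tailed *t* test, Mann-Whitney *U* test, or chi-square test") and to continuous variables at t1. The general statement "The significance level will be set at *P*<.05" is not tied to safety.

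Study Design gives an "allocation ratio of 1:1 for the intervention and waitlist control groups", but the Randomization section limits this: "Only the 30 participants recruited at the GSU will be block randomized". The other 15 of the 45 planned participants, at the clinic in Tübingen, are not randomised, and data collection there concentrates on the primary outcomes.

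**The concern.** The participant is the unit of randomisation, but the event is the unit counted. Three event types (autonomic dysreflexia, pressure ulcers and shoulder pain) are listed in advance as ones that "can occur because of physical strain or are common complications after SCI and are, therefore, classified as expected AEs or SAEs". If any of them recurs in one person within the six weeks, a total mixes two different things: how many people were affected, and how often each was. With about 15 people per arm, a single participant can then decide which group has more events.

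A total without a denominator also has no meaning across groups of different size, and the article does not say in which group, if any, the 15 non-randomised participants enter this comparison. At stake is the reading of a primary outcome: an apparent harm, or an apparent absence of one, that reflects one person or a difference in headcount.

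**Working it through.** **Inputs.**
- Randomised: 30 (Randomization) at 1:1 (Study Design), so about 30/2 = 15 per arm.
- Not randomised: 15 (Sample Size, Randomization).
- Event rate: no figure is given. Principal Findings expects adverse events to be rare.
- Recurrence within a person: not stated; assumed below.
- Test level 0.05, two-sided: assumed for illustration only, since the article ties neither to safety.

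The article gives no event rate, test or power for safety, so there is no figure of its own to reproduce.

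**Step 1: what a total can hide (15 v 15).** The event column tests the totals as if every event were independent: exact binomial, probability 1/2. The participant column is Fisher's exact test on people with at least one event.

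| Pattern | Events | P, events | Participants | P, participants |
|---|---|---|---|---|
| One person with 6 v none | 6 v 0 | 0.031 | 1/15 v 0/15 | 1.00 |
| Two people with 4 each v one event | 8 v 1 | 0.039 | 2/15 v 1/15 | 1.00 |
| Five people with 1 each v one person with 5 | 5 v 5 | 1.00 | 5/15 v 1/15 | 0.17 |

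Arithmetic:
- Row 1, events: 2 × 0.5^6 = 0.031.
- Row 2, events: 2 × (9 + 1)/2^9 = 20/512 = 0.039.
- Row 3, participants: 2 × [C(15,5)·C(15,1) + C(15,6)]/C(30,6) = 2 × (45,045 + 5,005)/593,775 = 0.169.

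The counts make the point without the P values: the same totals fit very different numbers of affected people.

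**Step 2: group size.** Expected events = people × rate. At an assumed 0.2 events per person in both groups, 30 v 15 people gives 30 × 0.2 = 6 v 15 × 0.2 = 3 events, twofold with no difference in risk. The 30 v 15 split applies only if all non-randomised participants are counted with the intervention group, which is an inference. Table 3 shows 8 v 4 at submission, so unequal group sizes are not hypothetical, although that is early enrolment only.

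**Step 3: how much recurrence could matter if totals were tested.** 20,000 simulated trials per setting, 15 v 15, no true difference. Events per person are Poisson with a gamma-distributed rate of mean m and shape k, so the variance exceeds Poisson by the factor 1 + m/k. All values of m and k are assumptions. False-positive rate at 5%:

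| m | No clustering | k = 1 | k = 0.5 | k = 0.2 | Participants (Fisher), all k |
|---|---|---|---|---|---|
| 0.2 | 1.1% | 2.2% | 3.3% | 6.7% | 1.0–1.5% |
| 0.5 | 2.7% | 6.8% | 11.3% | 22.5% | 1.6–2.1% |
| 1.0 | 3.1% | 12.6% | 21.2% | 36.4% | 1.6–1.7% |

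The row closest to the authors' expectation is the first, where the rate exceeds 5% only at the strongest clustering. With 30 v 15 and no clustering, testing raw totals as if the groups were equal gives 9.4% (m = 0.2) to 56.0% (m = 1.0). Fisher's test on participants gives about 3%.

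**The case against.** The strongest reply is that nothing in the article treats repeat events as independent. A reader might infer from the word *number* that event totals will go into a test assuming independent events, and so that the primary safety analysis has an inflated false-positive rate. The text does not support this. The comparison may be descriptive. If per-participant counts were tested, the method the article gives for skewed variables between groups is Mann-Whitney, whose unit is the participant. The rates in Step 3 therefore describe a test the protocol never names. This part of the objection stands in full.

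It also stands that recurrence within six weeks is assumed, that the authors expect few events, and that no success threshold rests on the total, unlike feasibility and usability. If only intervention-related events count, as in the Safety section, controls without the app may have few or none, and the equal-rate simulation does not describe that situation.

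It can be added that table layout and intervals normally belong in a fuller document. That is true of layout. But the article does state the quantity to be compared, and that stated quantity is the problem. In a pilot this small, a person with many events would be noticed in the records, but noticing is not the same as planning the comparison so that it shows.

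**Conclusion.** The point holds in limited form. The stated safety comparison is a raw event total per group. It does not show how many people were affected and has no denominator, which is a poor choice for a primary outcome with about 15 randomised per arm. Step 1 shows the size in concrete terms: 6 v 0 events can be one person, and a 5 v 5 tie can conceal 5/15 v 1/15. This rests on the assumption that events can recur in one person. At a rate as low as the authors expect, the effect is small unless recurrence is strongly concentrated.

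The denominator problem needs no such assumption, only groups of unequal size. A reader might also infer that the Tübingen participants will be added to the intervention total; the article does not say so, and 30 v 15 is only an example of what it leaves open. None of this shows an invalid primary analysis. It shows a stated quantity that is easily improved.

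**What to change.** Amend the safety sentence in Quantitative Analysis along these lines: *Among randomised participants, safety will be compared between groups as the number and proportion of participants with at least one study-related AE, and separately at least one study-related SAE, with the denominator for each group and the risk difference with an exact 95% CI. Total events and events per affected participant will be reported alongside. Events at the non-randomised site will be reported separately.*

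If an event rate is also compared, use person-weeks as the denominator and a variance that allows for repeat events within a person.

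The cost is wording only. Data are held by participant study ID (Data Management), so nothing new need be collected. The small downside is that a proportion does not use recurrence, which is itself safety information; the event totals beside it keep that. The intervals will be wide, as they should be: with 0 of 15 affected, the exact two-sided 95% upper limit for one arm is 1 − 0.025^(1/15) = 21.8%.
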